#### Outcome Measures

The outcome evaluation for this study will be based on data collected both at baseline and during the postintervention follow-up (after 6 months). Data collection tools will be identical for data collection at both periods and include information on patient’s demographics, disease history, lifestyle behaviors, medication use, primary use of health care services, and hospitalizations. Height, weight, waist circumference, glycosylated blood glucose levels, and blood pressure will also be measured.

The primary study outcomes will be blood pressure and blood glucose levels as well as levels of adherence to recommended lifestyle modifications. Other outcomes will include changes in medication adherence and additional health-related outcomes, such as frequency of hospitalization or the occurrence of complications.

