##### Lifestyle Modifications

Patients’ levels of adherence to recommended lifestyle modifications will be assessed using self-reported questions adapted from the Hypertension Self-Care Activity Level Effects Scale (H-SCALE) questionnaire. The H-SCALE is a validated self-reported questionnaire for assessing self-care practices for hypertension prevention and control [26]. The questionnaire assesses 5 key recommended lifestyle modifications (ie, low-salt diet, physical activity, smoking cessation, weight management, and abstinence from alcohol) as well as adherence to medication. Table 2 shows how each recommended lifestyle modification will be assessed based on the H-SCALE.

**Table 2 table2:** Assessment of lifestyle modifications using an interviewer-administered questionnaire adapted from the Hypertension Self-Care Activity Level Effects Scale (H-SCALE).

Recommended lifestyle modification	The WHO^a^ recommendation	Assessment method
Weight reduction and management	Maintain normal body weight (BMI 18.5-24.9 kg/m^2^)	First, the patient’s BMI will be assessed based on the patient’s height and weight. All patients with a BMI above 24.9 will be considered as overweight. Second, 10 questions will be used to assess activities undertaken to manage weight through dietary practices, such as reducing portion size, making food substitutions, and exercising to lose weight. Participants who say yes to 5 or more questions will be nonadherent to recommended weight management practices.
Reducing dietary salt intake	Reduce dietary salt intake to less than 2400 mg of sodium per day or less than 6000 mg sodium chloride per day.	A total of 6 questions will be used to assess practices related avoiding salt while cooking and avoiding foods high in salt content. Patients who answer yes to 3 or more questions will be considered as nonadherent to a low salt diet.
Reducing dietary fat intake	Avoid foods high in cholesterol and fat content	A total of 2 questions will be used to assess practices related to avoiding foods high in cholesterol and fat content. Patients who answer yes to any 1 question will be considered as nonadherent to a low fat or cholesterol diet.

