Increasing fruit and vegetable consumption	Consume 5 servings (equivalent of 5 tablespoons) of vegetables and 3 servings (equivalent of to at least 3 fruits) of fruits every day.	A total of 2 questions will be asked to assess adherence to fruits and vegetables. Patients who answer yes to any 1 question will be considered as adherent to a high fruit and vegetable diet.
Smoking	Avoid smoking	Smoking status will be assessed by 1 question. All patients who answer yes to the question will be considered nonadherent to nonsmoking recommendations
Moderation in alcohol consumption	Limit alcohol consumption to no more than 2 drinks (eg, 24 oz of beer, 10 oz of wine, or 3 oz of 80-proof whiskey) per day in men and no more than 1 drink per day in women and lighter-weight persons.	Alcohol intake will be assessed using 2 questions. Participants who answer yes to any 1 of the questions will be considered nonadherent to the alcohol recommendation moderation.
Physical activity	Engage in regular aerobic exercises, such as brisk walking for at least 30 minutes per day, for at least 5 days a week.	Physical activity will be assessed by 1 question. Participants who answer yes to the question will be considered as being adherent to the physical activity recommendation.

^a^WHO: World Health Organization.

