#### Data Analysis

Data analysis will be performed using the Epi Info (Centers for Disease Control and Prevention) software. The primary analysis will be conducted under the intention-to-treat principle. For individual outcomes, proportions will be compared using the chi-square test, and continuous measures will be compared using 2-tailed *t* tests. Stratified analysis will be conducted to control for confounding and assess the effect modification by demographic variables and medication adherence. The effects of the intervention will be tested by ANOVA, which will allow adjustment for baseline differences between groups. Two-sided *P* values and 95% CIs will be used to determine statistical significance of results.

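### Smoking and alcohol adherence are scored as current use in all participants and compared by chi-square with no term for baseline use, which costs precision that the baseline answers already collected could recover

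*Protocol article*

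**What the plan says.** Outcome Measures makes lifestyle adherence a primary outcome: "The primary study outcomes will be blood pressure and blood glucose levels as well as levels of adherence to recommended lifestyle modifications". The running text under Lifestyle Modifications lists the behaviours as "low-salt diet, physical activity, smoking cessation, weight management, and abstinence from alcohol". Table 2 then gives the scoring rules. For smoking: "All patients who answer yes to the question will be considered nonadherent to nonsmoking recommendations". For alcohol, where the recommendation is a daily limit ("Limit alcohol consumption to no more than 2 drinks" for men, with a lower limit for women and lighter-weight persons): "Participants who answer yes to any 1 of the questions will be considered nonadherent to the alcohol recommendation moderation". Both rules cover every participant, and the eligibility criteria do not require anyone to smoke or drink.

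Under Data Analysis, "proportions will be compared using the chi-square test". The same section says that intervention effects will be tested by ANOVA, which is said to permit adjustment for baseline differences, and that stratified analyses will use demographic variables and medication adherence. Neither sentence names baseline smoking or drinking. Outcome Measures bases the evaluation on both visits and adds: "Data collection tools will be identical for data collection at both periods". Each participant's baseline status is therefore on file.

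**The concern.** A participant who did not smoke, or was not over the alcohol limit, at baseline is already scored adherent. That participant can only stay the same or get worse. Only baseline users can show the benefit that the intervention aims at, yet the chi-square spreads their response over everyone.

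Two things follow. First, the difference between arms is diluted by the share of users. Second, use tends to persist, so much of the variation in the 6-month proportions is inherited from how many users each arm had at the start. With 14 clinics allocated by simple randomization, that number can differ appreciably by chance. A real effect on quitting could be missed in two components of a primary outcome, although data that would sharpen the comparison are in hand. High adherence in both arms would also say little about whether behaviour changed.

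**Working it through.** **Inputs from the protocol article.** 7 clinics per arm, 49 participants per clinic, 20% loss: 49 × 0.8 = 39.2, so m = 39 analysed per clinic and 7 × 39 = 273 per arm. The plan gives no prevalence, quit or power figure for smoking or alcohol, so there is none to reproduce.

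**Assumptions.** Baseline share scored nonadherent ("users") p = 5-30%; clinic-to-clinic coefficient of variation (CV) of that share 0.2-0.4; new use among non-users u = 1-5%; quitting q = 10% in control v 30% in intervention.

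**Dilution.** Expected use at 6 months is p(1 − q) + (1 − p)u, so the arm difference is p × (q in intervention − q in control). The 20-point difference in quitting becomes 0.05 × 20 = 1 point at p = 5%, 2 points at 10%, 4 points at 20% and 6 points at 30%.

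**Baseline noise.** The variance of the chance arm difference in baseline use is (2/7) × [(CV × p)² × (38/39) + p(1 − p)/39]. At p = 20%:
- CV 0.2: (2/7) × (0.00156 + 0.00410) = 0.00162, SD 4.0 points.
- CV 0.4: (2/7) × (0.00624 + 0.00410) = 0.00295, SD 5.4 points.

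The chance baseline difference is thus as large as the 4-point effect sought.

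**Unconditional v conditional standard error, no effect (q = 10% in both arms).** A fraction (1 − q − u) of the baseline difference carries over to 6 months. The variance left after conditioning on own baseline status is (2/7) × [p·q(1 − q) + (1 − p)·u(1 − u)]/39. At p = 20%, u = 1%:
- Conditional: (2/7) × (0.0180 + 0.0079)/39 = 0.000190, SE 1.4 points.
- Unconditional, CV 0.2: 0.89² × 0.00162 + 0.000190 = 0.00147, SE 3.8 points, ratio 2.8.
- Unconditional, CV 0.4: 0.89² × 0.00295 + 0.000190 = 0.00253, SE 5.0 points, ratio 3.7.

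The same formula at the corners of the assumed range gives 1.3 (p = 5%, CV 0.2, u = 5%) and 4.3 (p = 30%, CV 0.4, u = 1%). Simulation gives about 1.3 to 4.4 under no effect and 1.2 to 3.0 with the effect.

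**Power, simulated with a clinic-level t test on 12 degrees of freedom.** The conditional version uses clinic means of residuals after predicting each participant's 6-month status from baseline status.

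| Prevalence | New use 1%: unconditional v conditional | New use 5%: unconditional v conditional |
|---|---|---|
| 10% | about 10% v 26% | 8-10% v 14% |
| 20% | 11-18% v 55-58% | 12-16% v 35% |
| 30% | 13-24% v 76-80% | 14-23% v 59-61% |

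At 5% prevalence both are low (about 7% v 12-13% with 1% new use). With 5% new use the conditional SE is √[(2/7) × (0.0045 + 0.0451)/39] = 1.9 points against a 1-point effect, so there is little to gain.

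**If status fluctuates**, as drinking over a daily limit may (assumed: 40% of control users come within the limit, 10% of others exceed it, same 20-point difference), the SE ratio under no effect is only about 1.1 to 1.5. Power is 9% v 10% at 10% prevalence, 16-18% v 22-23% at 20%, and 23-30% v 39-41% at 30%.

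**The case against.** The strongest reply is that the plan already provides for baseline. The evaluation is based on both visits, and the ANOVA sentence mentions baseline adjustment without limiting it to continuous measures. It is also true that Table 2 does not say the contrast uses 6-month status alone; that is inferred from a scoring rule that applies equally at both visits. These points soften the concern but do not remove it. The only test that the section assigns to proportions is the chi-square, the ANOVA is not tied to the yes/no items and is not suited to them, and no sentence names baseline smoking or drinking as a term.

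A second reply is that Table 2 is coherent: a never-smoker does adhere to advice not to smoke, and comparing current status in all participants is valid under randomization. That stands. The expected baseline difference is zero, so a reader who infers systematic bias goes further than the documents allow.

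A reader might also infer that the chi-square mainly compares how many users each arm started with. That depends on prevalence and persistence figures that the documents do not give. It fits stable use with a small effect, and fits poorly with high prevalence and a large effect or with fluctuating drinking. The two alcohol questions are in an appendix that is not shown, so how many participants could respond on that item cannot be judged.

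Finally, the patient-level chi-square rejects too often under no effect when clinics differ. That comes from ignoring clustering: the clinic-level test of the same unconditional status rejects 4.7-5.2%. It is not part of this point.

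**Conclusion.** The point holds as one of dilution and avoidable loss of precision in two components of a primary outcome. The scoring rule and the chi-square are both stated, and neither uses the participant's own baseline answer. Under the assumed ranges, ignoring that answer multiplies the standard error by about 1.3 to 4.4 under no effect (1.2 to 3.0 with the effect), and conditioning on it raises power at 20% prevalence from about 11-18% to 35-58%. The gain is small at 5% prevalence and, if status fluctuates, small at 10-20% prevalence too. All of these sizes rest on assumed prevalence, clinic variation, persistence and quitting; only the clinic numbers and the loss rate come from the protocol.

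It does not follow that the all-participant definition is invalid, that the result would be biased, or that the plan certainly ignores baseline. An analysis plan that is not shown may settle the last of these.

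**What to change.** State that, for the smoking and alcohol components, the deciding comparison is 6-month status conditional on the participant's own baseline status, keeping all participants and allowing for clinic. A clinic-level analysis of residuals, or a binary model with baseline status as covariate and clinic taken into account, would serve. Say explicitly whether the ANOVA sentence is meant to cover the yes/no items.

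Beside it, report descriptively by arm the share of baseline users who quit or came within the limit, and the share of baseline non-users who started.

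Keeping all participants removes baseline noise but leaves the definition and denominator as they are, so the effect remains an all-participant one. The descriptive shares show the change in behaviour directly.

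The cost is a few sentences and one table, with no new data, visits or participants, because the same tool is used at both visits. The downside is wide intervals for the quit shares: at 10% prevalence there are only about 27 baseline users per arm (273 × 0.10).

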##### Hypertension and Diabetes Control

Patient’s hypertension and diabetes control will be assessed by blood pressure and HbA_1c_ measurements, respectively*.* Blood pressure of 140/90 mm Hg or higher will be considered uncontrolled hypertension, while an HbA_1c_ level above 8% (53 mmol/mol) will be considered uncontrolled diabetes [27].

##### Adherence to Medication

Patients’ adherence to medication will be assessed using a widely used and validated tool, the 8-item Morisky Medication Adherence Scale (MMAS-8) [28-31]. The MMAS-8 consists of 8 questions that assess patients’ adherence to medication. Patients who score 8 points on the MMAS-8 will be considered to have high adherence, and patients who score 7 and 6 will be considered to have medium adherence; those scoring less than 6 points will be classified as having low adherence.

##### Other Health Outcomes

Other health outcomes, such as hospitalization and the occurrence of diabetes and hypertension complications, will be assessed from the patients’ clinic records*.*

##### Sample Size

Based on the recommendations for sample size calculation for cluster randomized controlled trials with a fixed number of clusters [32], a total of 680 participants will be required for the trial. Therefore, the study will comprise 14 clusters, with 49 participants per cluster. The sample size was calculated using the following parameters, obtained from the review of literature: 80% study power, 0.5 effect size, 1 SD, 0.05 coefficient of variation, and 20% lost to follow-up adjustment.

##### Data Collection and Management

Recruitment of participants started in June 2023. Baseline data were collected during the recruitment of participants. Follow-up data will be collected after 6 months, in January 2024. Data will be collected using the research assistants’ smartphones. The questionnaire will be uploaded onto the phones and the REDCap platform will be used for storing and managing the data. The computer system that will be used for storing the data will be password protected so that the data will only be accessible to authorized individuals. Patients will be assigned unique identifying numbers at the beginning of the study and the same number will be used in the follow-up data collection period. Data will be managed according to the International Conference on Harmonisation Guidelines for Good Clinical Practices [33]. To minimize errors, range checks and skip patterns within data entry screens will be used. Data will be backed up on a password-protected external hard drive as well as on Google Drive.

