## Methods

### Study Design

The study is a cluster randomized controlled trial, which will be conducted in the city of Harare in Zimbabwe from June 2023 to January 2024. The design, implementation, and reporting of the study are based on the recommendations from CONSORT (Consolidated Standards of Reporting Trials) statement on cluster randomized controlled trials [23]. The cluster randomized controlled trial will have a 6-month follow-up period and will consist of 1 intervention arm and 1 control arm.

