In terms of content, in the first session, the CHW will educate the patient on the recommended lifestyle modifications and the consequences of nonadherence. In the second session, focus will be on the patient’s barriers to adopting recommended lifestyle modifications and ways to overcome them. At the end of this session, patients are expected to write down their own plan for lifestyle modifications on a card, which they will then place in a visible location in their home. This will serve as a cue to action. The second session will be highly interactive, compared to the first session. The third and fourth sessions will be supportive and evaluation sessions during which the CHW assesses whether the patient has been following the action plan established in the second session. In the fourth session, which will be conducted at home, available family members will be involved to support the patient, and this will serve as another cue to action for the patient and will also help to build the patient’s self-efficacy. Any deviations from the plan will be discussed and ways to correct will be explored. The monthly home visits conducted after the fourth educational session will serve as support visits, where the CHW will continue to reinforce the importance of adhering to lifestyle modifications.

In terms of timing, the first session will be conducted on the day of recruitment, and the second session will be scheduled a week after the first session. The third session will be conducted 2 weeks after the second session, and the fourth session will also be conducted 2 weeks after the third session. A month after the fourth session, the patients will receive monthly home visits at a date and time convenient for them. Each educational session will last 45-60 minutes, while the monthly support visits will last 10-15 minutes.

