#### Recruitment of Participants

Participants will be recruited by trained research assistants every day of the 1-week recruitment period. The recruitment process will be done concurrently at control and intervention sites. Baseline data will be collected on the day of the recruitment, and research assistants will not be aware of group allocations during the recruitment and the baseline data collection periods.

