## Results

Recruitment of study participants commenced on June 1, 2023, and was completed on July 30, 2023. Baseline data are being collected after participant recruitment, and the final data collection will be completed by January 31, 2024.

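### Follow-up collected only in January 2024 cannot be 6 months for patients recruited from 1 June to 30 July 2023, and the order of baseline and session 1 is not stated

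*Protocol article*

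**What the plan says.** **Length of follow-up.** Study Design states: "The cluster randomized controlled trial will have a 6-month follow-up period". Outcome Measures likewise has two assessments, at baseline and after 6 months, and calls the second one postintervention. The Abstract says that the intervention itself runs over 6 months.

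**Calendar of follow-up.** Data Collection and Management: "Follow-up data will be collected after 6 months, in January 2024". The Results section adds that "the final data collection will be completed by January 31, 2024".

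**Recruitment.** The Methods, under Recruitment of Participants, say: "Participants will be recruited by trained research assistants every day of the 1-week recruitment period". The same section has control and intervention sites recruiting at the same time. The Results section (and the Abstract) report: "Recruitment of study participants commenced on June 1, 2023, and was completed on July 30, 2023".

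**Baseline and session 1.** Recruitment of Participants: "Baseline data will be collected on the day of the recruitment". Data Collection and Management puts baseline during recruitment, in the past tense. The Results section, in the present tense: "Baseline data are being collected after participant recruitment". In the intervention arm, "the first session will be conducted on the day of recruitment". No section says which of the two comes first.

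**The concern.** Collection in a single month suits a short recruitment period one half-year earlier. It does not suit 60 days of recruitment. The primary outcomes (blood pressure, blood glucose and lifestyle adherence) would be reported as 6-month results although many patients are measured later. Some would be measured well after the 6-month intervention has ended and others at its end, so the result would average over different times since the last support visit.

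The second strand concerns baseline. The Data Analysis section adjusts for baseline differences between groups. That adjustment is sound only if baseline precedes any intervention contact. Session 1 falls on the day of recruitment, so a baseline taken after it would be a pre-treatment value in the control arm only, and adjusting for it could remove part of an early effect.

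**Working it through.** **Inputs, all from the protocol article.** Recruitment 1 June to 30 July 2023 (Abstract and Results). Follow-up collection in January 2024 (Data Collection and Management), closing on 31 January (Results). Stated follow-up 6 months (Study Design, Outcome Measures). One month is taken as 365.25 / 12 = 30.4375 days.

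**Step 1: can the stated 6 months be reproduced?** Recruitment spans 60 calendar days, 30 in June and 30 in July. Six months after 1 June is 1 December 2023; six months after 30 July is 30 January 2024. Exact 6-month visits would therefore run from 1 December to 30 January. Only the July recruitment days (30 of 60) have their 6-month date in January. All 30 June days have it in December. The stated figure is not reproduced for June recruits.

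**Step 2: interval by recruitment date**, as days from recruitment to collection divided by 30.4375.

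| Recruited | Seen 1 January 2024 | Seen 31 January 2024 |
|---|---|---|
| 1 June | 214 days, 7.03 months | 244 days, 8.02 months |
| 30 June | 185 days, 6.08 months | 215 days, 7.06 months |
| 1 July | 184 days, 6.05 months | 214 days, 7.03 months |
| 30 July | 155 days, 5.09 months | 185 days, 6.08 months |

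**Step 3: what the wording allows.**

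- Taking 6 months as a minimum, no July recruit is seen before the same date in January (184 days). The range is 184 to 244 days, about 6.0 to 8.0 months, a spread of 60 days.
- If patients are also seen in the order in which they were recruited, the range narrows to 214 days for the first and 185 days for the last, about 7.0 down to 6.1 months.
- If the minimum is not kept and late-July recruits are seen early in January, the lower end falls to 155 days, 5.1 months.

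**Step 4: does the 1-week recruitment period rescue the plan?** A week starting on 1 June gives 6.8 to 8.0 months. A week starting on 24 July gives 5.1 to 6.3 months. A week in July would suit January collection, because every July date has its 6-month date in January, but the reported dates do not describe one.

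**Step 5: baseline against session 1.** No arithmetic applies. The Methods put baseline and session 1 on the same day without an order. Data Collection and Management has baseline taken during recruitment and finished. The Abstract and Results have it taken after recruitment and still in progress. If those last two mean that baseline came on a later day than recruitment, it came after session 1 in the intervention arm. If they mean only that each patient is enrolled and then measured, they fit the Methods apart from the tense. Neither reading settles the order within the day.

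**The case against.** The case for the plan has four parts.

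First, the sentence on follow-up says after 6 months, so a visit at 5.1 months would break the plan rather than follow it. This stands: the 5-to-8-month range is an outer envelope that pairs the earliest recruit with the last day and the latest recruit with the first. It leaves untouched the fact that June recruits are all past 6 months when collection opens.

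Second, recruitment is concurrent across arms, so the spread in follow-up should be similar in both. This also stands. A reader might suppose that clinics were recruited one after another, a week each, which would reconcile one week with 60 days and turn the interval into a clinic-level difference that 7 against 7 clinics might not balance. No section says so.

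Third, the Randomization and Recruitment sections keep data collectors unaware of allocation until baseline is complete, which suggests that baseline precedes any intervention session, and the present-tense Results sentence may be only a status line. This is a fair reading. It makes a baseline before session 1 plausible but does not state it.

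Fourth, a condensed article may leave visit windows to the full protocol. That is accepted, and the absence of a window is not the point. The point is that the dates the article does give conflict with one another.

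**Conclusion.** The point holds as an inconsistency of timing. With recruitment from 1 June to 30 July 2023 and collection confined to January 2024, follow-up is about 6 to 8 months, not 6. Patients recruited on 1 June are measured at 7.0 to 8.0 months, up to two months after a 6-month intervention would have ended. The lower end reaches 5.1 months only if the 6-month minimum is not observed. The 1-week recruitment period in the Methods contradicts the 60 days reported in the Results.

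The consequence is extra variability in the outcome and a time label that does not describe the data. Between-arm bias is possible but not shown, given concurrent recruitment.

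On baseline, a reader might infer that the documents disagree on whether it preceded session 1, or that it was contaminated by session 1 in the intervention arm. They support neither. They describe baseline timing in ways that do not clearly agree, and they leave its order relative to session 1 unstated. Any loss of effect through baseline adjustment is therefore conditional and cannot be sized.

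These conclusions assume that the reported recruitment dates are right and that follow-up is counted from enrolment.

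**What to change.** - Open follow-up on 1 December 2023 and see each patient at 6 months from their own enrolment, or within a short fixed window after it, with the same rule in both arms. Record the actual interval.
- Record the dates and order of baseline and session 1, and use as the baseline covariate only values taken before session 1.
- Reconcile the Abstract, Recruitment of Participants, Data Collection and Management, and Results to one timeline covering the length of recruitment, the timing of baseline and the follow-up dates.
- If January collection is kept, restate follow-up as about 6 to 8 months throughout.

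**Cost.** Field work starts a month earlier, with no extra visits. Visits exactly at 6 months end on 30 January and fit the present close. A window after 6 months moves the close slightly: 14 days, for illustration, would take the last recruits to 13 February. The article is dated 3 October 2023, so a 1 December opening was still practicable at publication.
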